**Emotional status**

We will use an Arabic-validated version of the Hospital Anxiety and Depression Scale **(HADS)** to assess anxiety and depression in our patients [11]. The HADS is a 14-item questionnaire specifically developed to gauge anxiety and depression in non-psychiatric populations. It comprises two subscales, one for depression and the other for anxiety, each consisting of 7 items. Based on the relative frequency of symptoms over the past week, the respondent rates each item on a 4-point Likert scale ranging from 0 (no impairment) to 3 (severe impairment). The total score is derived by summing responses of all 14 items resulting in a total score ranging from 0 to 21 for each subscale. Scores of 11 or more on either subscale indicate significant symptoms, while scores of 8–10 indicate ‘borderline’ and 0–7 indicate ‘normal’.

**Cognitive function**

We will use a validated Arabic version of the Montreal Cognitive Assessment **(MoCA)** to evaluate the cognitive status of our patients [12]. The MoCA is a widely used tool for early screening for mild cognitive impairment **(MCI)** in the general population. It assesses various cognitive domains, including orientation, memory, attention, language, executive function, and visuospatial function. These domains are evaluated using tasks such as naming three uncommon animals, recalling five words, performing a simple Trail Making Test Part B, and copying a cube and other items. The total MoCA score, obtained by adding points from each completed task, ranges from 0 to 30 points, with higher scores indicating better cognitive functioning. Patients with a score of 25 or lower are suspected of having cognitive impairment.

**Insomnia**

Insomnia will be evaluated using a validated Arabic version of the Insomnia Severity Index **(ISI)** [13]. The ISI consists of seven self-report items aimed at assessing various aspects of insomnia, including the severity of sleep onset, maintenance, and early morning awakening problems, as well as sleep dissatisfaction, interference with daytime functioning, noticeability of sleep problems by others, and distress related to sleep difficulties. Each item is rated on a 5-point Likert scale resulting in a total score of 0–28, with higher scores indicating more severe insomnia. Participants are classified as having a high risk of insomnia if their ISI score is 15 or higher.

**Excessive daytime sleepiness**

The study will use a validated Arabic version of the Epworth Sleepiness Scale **(ESS)** to measure daytime sleepiness over the past 3 months [14]. The ESS is an 8-item questionnaire where participants rate their likelihood of dozing off or falling asleep in various everyday situations on a 4-point Likert scale of 0–3. The total ESS score, calculated by summing all 8 item scores, ranges from 0 to 24, with higher scores indicating more severe daytime sleepiness. In this study, EDS is defined as an ESS score of 11 or higher, while severe EDS is defined as an ESS score of 16 or higher.

### 2.4. Therapeutic patient education

#### 2.4.1. Strategy.

To achieve our main objective, which is optimal adherence to CPAP, our TPE strategy focuses on explaining to the patient his disease and the benefit of being treated, leaving the principle that the better the patient understands, the better he will adhere to his treatment. In addition, the educational team will be provided with a detailed schedule for each TPE session indicating the order and timing of different workshops. The idea is to provide all patients with a common TPE program through a patient-centred approach.

The different TPE workshops were built through meticulous preparation by the educational team. Workshop topics were determined based on the identified obstacles to CPAP use. These obstacles included mainly the non-understanding of the diseases and the benefit of being treated, chronicity-dependence (trouble getting used to wearing the CPAP mask), having trouble properly fitting his CPAP mask, and side effects of CPAP.

#### 2.4.2. Team.

The educational team will include a sleep disorders specialist, a sleep nurse, and a CPAP technician.

#### 2.4.3. Tools.

For TPE at the hospital, we will use a short educational video (duration 10 minutes (min)) presenting a wide range of medical information in realistic clinical scenarios. The video script was written in Arabic Tunisian dialect through storytelling techniques to simplify medical jargon and help patients in fully comprehend their disease and the treatment they will receive (Video 1).

The video aims to provide patients with clear information about the OSAHS mechanism, risk factors, symptoms and complications. We will also use a before-after scenario to show patients the benefits of CPAP adherence by highlighting before and after CPAP effects. The video also offers tips to help patients adjust to using a CPAP machine and shows how using a CPAP machine will get easier over time. Additionally, the video explains the common side effects of CPAP and what patients can do to manage them.

To follow up on the TPE at home, every patient will be provided with a daily desk calendar and 1 tip on CPAP therapy on each sheet (Video 2). This strategy of daily reminders through brief sayings or phrases will serve as a proactive communication tool to keep patients informed and engaged in their healthcare journey.

#### 2.4.4. Education location.

During TPE sessions, patients will gather in a spacious, calm room with light and airy wall colours: white and cream. The room is furnished with a flat-screen high-definition television, a board, flexible chairs, and wireless internet. The chairs are arranged in a U-shape so that patients can face each other, while the health provider can move around the room.

#### 2.4.5. Educational session program.

As shown in Table 1, the TPE session will start at 9:00 AM and usually last for about 3 hours. Patients are expected to bring their CPAP devices with them. Upon arrival, they will be greeted by the sleep nurse, after which the day’s agenda will be presented and the therapeutic education team introduced. Patients will be then encouraged to share their expectations for the session.

**Table 1 pone.0322285.t001:** TPE session schedule at the hospital CPAP initiation.

**09:00 am** Reception of patients
**09:10 am** Introduction of therapeutic educational teal and day’s agenda to patients
**09:20 am** Video-projection
**09:50 am** W1:” What’s OSAHS”
**10:05 am** W2: “CPAP machine: what is it? How does it work? And what does it serve for?”, Each patient disassembles, cleans, and reassembles his CPAP device.
**10:35 am** W3: “How to use your CPAP and fit your mask” Each patient wears his CPAP mask for at least 20 min.
**11:05 am** W4: “How to deal with CPAP side effects”
**12:00 pm** Return home with CPAP device and educational support. Each patient is provided with educational support (desk Calander and educational documents provided by the manufacturer).

TPE: therapeutic patient education. CPAP: continuous positive airway pr” pressure. W: workshop.

The TPE session program will include 4 workshops entitled: “What’s OSAHS”, “CPAP machine: what is it? How does it work? And what does it serve for?”, “How to use your CPAP and fit your mask” and “How to deal with CPAP side effects”.

All workshops will combine video demonstrations with live presentations. As a result, each patient will be invited to disassemble, clean, and reassemble his CPAP device. Patients will be then acclimated to wear the CPAP mask for at least 20 min during the TPE session. All these activities will be supervised and guided by a CPAP technician.

### 2.5. Usual care

Patients assigned to the usual care group will undergo CPAP initiation at home under the guidance of a trained CPAP technician. The initiation session will last 30–40 min and include an oral explanation of OSAHS and CPAP therapy and a brief demonstration of CPAP device usage. These patients will not receive additional educational support beyond the documents provided by the manufacturers and will have no direct contact with investigators before the 1-month follow-up appointment.

### 2.6. Protocol study

After a nocturnal polygraph recording showed severe OSAHS, the patient will be seen by a sleep doctor the following day. The doctor will explain the diagnosis and the need for CPAP therapy. The patient will then complete an informed consent form to participate in the study and be randomly assigned to either the usual care (n = 30) or the TPE group (n = 30). Additionally, the patient will fill out a questionnaire covering sociodemographic data, health status, NOSE questionnaire, WHO-5 questionnaire, HAD questionnaire, FSS questionnaire, MoCA questionnaire, ESS questionnaire and ISI questionnaire. Following this, the patient will be scheduled to start CPAP therapy within 1–2 weeks after the nocturnal polygraph recording.

Following the TPE session, patients in the TPE group will be provided with CPAP devices to take home. They will be advised to call the sleep nurses if they experience any side effects. The phone line will be available on weekdays from 9:00 am to 4:00 pm, and patients can leave a message at other times. An assigned nurse will contact patients on the second and fifteenth days to identify and resolve any CPAP-related issues. The SDC CPAP Questionnaire will be administered by the nurse for each patient in this group on day 2 following CPAP titration.

Patients in the usual care group will be advised to consult the CPAP technician for any questions or concerns.

Both groups of patients will be scheduled for follow-up appointments with a CPAP technician and a sleep physician on day 15 (only if the CPAP perception score is poor) and at 1, 3, and 6 months after starting CPAP therapy. During each visit, we will assess adherence to and tolerance of CPAP by asking questions about side effects and reviewing CPAP SD Card data. Any CPAP-related issues reported by the patients will be addressed accordingly. At the 6-month follow-up, all patients will be asked to complete the functional outcomes questionnaires once again (Figs 1 and 2). Sleep physicians involved in the routine clinical follow-up of the patients will be blinded to each patient’s treatment group.

**Fig 1 pone.0322285.g001:**
[figure not shown]
SPIRIT schedule of enrollment.

**Fig 2 pone.0322285.g002:**
[figure not shown]
Flow diagram of the study protocol. OSAHS: obstructive sleep apnea-hypopnea syndrome. NOSE: Nasal Obstruction Symptom Evaluation. WHO5: World Health Organization- Five Well-Being Index. FSS: Fatigue Severity Scale. HADS: Hospital Anxiety and Depression Scale. MoCA: Montreal cognitive assessment. ISS: Insomnia Severity Index. ESS: Epworth Sleepiness Scale. CPAP: Continuous Positive Airway Pressure. SE: Side Effects. SDC CPAP Questionnaire: Sleep Disorders Center CPAP Questionnaire. M: Month.

### 2.7. Statistical analysis

The data analysis will be conducted using SPSS Statistics for Windows, Version 23.0 (IBM SPSS Statistics for Windows, Version 23.0. Armonk, NY: IBM). We will use the Kolmogorov-Smirnov test to assess the normal distribution of data. Continuous variables with a normal distribution will be expressed as mean and standard deviation **(SD)**, while non-normally distributed variables will be represented as median and interquartile range **(IQR)**. For comparing means of 2 and 3 or more categories of normally distributed continuous variables, independent Samples t-test and ANOVA test will be used, respectively. Medians of non-normally distributed continuous variables will be compared using non-parametric tests (Mann-Whitney U test and Kruskal-Wallis). Categorical variables will be presented as counts and frequencies. The frequencies of categorical variables will be compared using Pearson χ2 or Fisher’s exact test, as appropriate. A significant level of p < 0.05 will be considered.

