### 2.2. Patients

All patients referred to the Department of Respiratory and Sleep Medicine at Hedi Chaker University Hospital of Sfax-Tunisia, for suspected OSAHS will be screened for eligibility between January 2025 and July 2025. Sixty patients will be included. The study will be terminated by December 31^st^, 2025.

Patients will be determined eligible if they are aged 18 years old and above and newly diagnosed with severe OSAS (obstructive apnea-hypopnea index **(OAHI)** ≥ 30 events/ h) as revealed by an overnight type III polysomnography **(PSG)**.

Patients who have previously received CPAP therapy will not be included in the study. Additional exclusion criteria are refusal to participate, illiteracy, pregnancy, major mental disorders, severe heart failure with systolic fraction ejection **(SEF)** < 45%, severe neuromuscular diseases and oxygen supplementation.

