#### 2.3.4. Outcome measures.

Our prespecified primary outcome is CPAP adherence measured in h/night at 1, 3, and 6 months after starting CPAP therapy. Our secondary outcome is functional status at the 6-month follow-up, which includes snoring, nasal obstruction symptoms, subjective quality of life, fatigue, emotional status, cognitive function, insomnia and EDS.

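### A normality pre-test on the trial's own data decides whether the primary adherence effect is a mean or a rank/median comparison, and only independent-group tests are listed for an outcome measured three times

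*Protocol article*

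**What the plan says.** Section 2.3.4 of the protocol article defines the primary outcome: "Our prespecified primary outcome is CPAP adherence measured in h/night at 1, 3, and 6 months after starting CPAP therapy". No single visit is singled out as primary.

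Section 2.7 gives one rule for all continuous variables. It begins with the gate: "We will use the Kolmogorov-Smirnov test to assess the normal distribution of data". Variables judged normal are summarised by mean and SD, "while non-normally distributed variables will be represented as median and interquartile range". The tests follow the same split. For two groups, or three or more groups, of normal data, "independent Samples t-test and ANOVA test will be used, respectively". Otherwise, "Medians of non-normally distributed continuous variables will be compared using non-parametric tests (Mann-Whitney U test and Kruskal-Wallis"). The threshold is stated once: "A significant level of p < 0.05 will be considered".

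The section does not exempt the primary outcome from the gate. ANOVA and Kruskal-Wallis are attached to the number of categories being compared, not to repeated visits. Section 2.2 fixes the size: "Sixty patients will be included". Section 2.6 splits them 30 and 30.

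**The concern.** Three things in this rule do not suit the primary outcome.

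- **The effect measure is not fixed in advance.** Whether the trial reports a mean difference or a median with a rank test depends on a pre-test of the data being analysed. Nothing in the text requires the same answer at months 1, 3 and 6.
- **The tests do not match the data structure.** Each patient contributes three correlated values, but only independent-group comparisons are named.
- **The rank test is described as comparing medians.** Mann-Whitney tests whether a value from one arm tends to exceed a value from the other. That is a comparison of medians only if the two distributions differ by a pure shift. Moving some patients out of very low use is not a pure shift.

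At stake is a primary result that reads the same way across visits and can be set beside the earlier trials in the Background, which are quoted as differences of 1.5, 1.7 and 2.0 h/night. A median and IQR with a Mann-Whitney p-value gives no such difference with a confidence interval.

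**Working it through.** **Inputs from the document:** 30 per arm, three visits, alpha 0.05 per test, and the gate and tests above. The document gives no SD, distribution, between-visit correlation or planned effect, so there is no figure of its own to reproduce. Everything below on shape, correlation and two-sidedness is assumed.

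**1. How often would the visits get different tests?** Simulated trials had 30 per arm, no true effect and between-visit correlation 0.5 to 0.85. The gate was applied at 0.05 at each visit, followed by a t-test if not rejected and Mann-Whitney if rejected. Corrected means that the critical value allows for an estimated mean and SD (Lilliefors).

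| Assumed shape of h/night | Corrected, pooled n = 60 | Corrected, per arm n = 30 | Uncorrected, pooled |
|---|---|---|---|
| Normal | 14% | 25–26% | about 0% |
| Limited to 0–9 h | 12–13% | 21–22% | about 0% |
| 15% near-zero users | 23–25% | 50–55% | 23–25% |
| Left-skewed | 46–53% | 48–53% | about 1% |

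A harsher assumption has low users near 0.7 h making up 15%, 20% and 25% at months 1, 3 and 6, the rest N(5.2, 1.5) h, and correlation 0.7. It gives about 57–65% with the correction and about 14–17% without. The overall range is therefore about 0% to 65%.

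**2. Do mean and median tell the same story?** Take the same mixture, with low users falling from 25% to 10%.

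- Means: 0.25 × 0.7 + 0.75 × 5.2 = 4.075 h, and 0.10 × 0.7 + 0.90 × 5.2 = 4.75 h. Difference 0.675 h.
- Medians, with low users all below the median: Φ((m − 5.2)/1.5) = (0.5 − p)/(1 − p).
  - p = 0.25: 0.25/0.75 = 0.333, z = −0.431, m = 4.554 h.
  - p = 0.10: 0.40/0.90 = 0.444, z = −0.140, m = 4.990 h.
  - Difference about 0.44 h.

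The same change would be summarised as about 0.68 h or 0.44 h, depending on the gate.

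**3. Does the gate damage type I error?** In the step 1 simulations, error per visit was 0.046–0.054. Under the uncorrected gate, which nearly always leaves the t-test in place, it was 0.048–0.054. So the t-test did not need the gate's protection under these shapes.

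**4. Do the two tests disagree?** Under no effect, they gave different verdicts at 0.05 in about 2% of visits. With low users falling from 25% to 10%, it was about 6–8% of visits, with power 0.20–0.22 (t-test) against 0.16 (Mann-Whitney). Counting any of the three visits, about 12–15% of trials had at least one disagreement.

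**5. What is lost by ignoring the repeated measures?** With complete data, a mixed model with arm, visit, arm × visit and unstructured covariance gives the same point estimate at month 6 as the simple difference in arm means. The gain comes when some visits are missing, because earlier values then inform later ones, and when a contrast spans visits. The document gives no basis for putting a number on it.

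**The case against.** The strongest reply is that section 2.7 is a generic paragraph in a condensed article. It never mentions visits, and a separate analysis plan may hold a longitudinal model. One normality judgement for h/night, applied at all visits, would also fit the words. That is fair: visit-by-visit gating is something a reader might infer, and the text permits it rather than states it. But a single judgement would still leave the effect measure to the data, and the rule is stated positively for all continuous variables. A mixed model in another document would have to override that rule, not merely add to it.

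Other stronger readings also go beyond the text:

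- **A coin flip.** A reader might infer that passing the gate is close to even odds. That holds only under particular assumed shapes with a corrected test. Section 2.7 names no variant, and no section describes the distribution of CPAP hours.
- **Missing visits.** A reader might infer that the plan drops patients with a missing visit. No such rule is stated, and the article may leave it to the full plan.
- **An uninterpretable time course.** This is too strong, since device hours can be summarised either way at every visit.
- **Inflated error from the pre-test.** The figures do not show this. The chance of at least one significant visit under no effect is about 0.09–0.13 (1 − 0.95³ = 0.143 if visits were independent), but that comes from three unadjusted tests and is a separate matter.

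Speaking of medians for Mann-Whitney is common shorthand and minor on its own. It matters here because the plan also switches the reported summary to medians.

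**Conclusion.** The point holds in this limited form: for the primary outcome, section 2.7 fixes a data-dependent choice of summary and test, and names only independent-group tests for a quantity measured three times. Depending on assumptions the document does not settle, the visits would receive different tests in about 0% to 65% of trials. Under one assumed fall in low users, the reported effect would be about 0.68 h as a mean or 0.44 h as a median, and the two tests would disagree at one or more visits in about 12–15% of trials. The efficiency loss is real when visits are missing but cannot be quantified from the document. False-positive risk at each visit is not materially affected. This should be corrected, but it does not undermine the trial's design.

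**What to change.** In section 2.7, exempt the primary outcome from the normality gate and prespecify:

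- **Effect measure:** the difference between arms in mean h/night, with 95% CI.
- **Model:** one linear mixed model on all randomised patients, with arm, visit and arm × visit as fixed effects and unstructured covariance across the three visits.
- **Primary contrast:** one named in advance, for example month 6, with the other visits reported from the same model.
- **Sensitivity analysis:** Mann-Whitney, described as a rank comparison, or a permutation test.

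Medians and IQRs can still be shown descriptively at every visit in both arms, whatever the shape.

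The cost is a rewording of section 2.7. Patients, visits and data collection do not change, and the model is available in the SPSS version already named (23). The one drawback is an analysis slightly less familiar to clinical readers than a t-test.

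### Seven functional scales are collected at enrolment and at month 6, but the between-group tests named for continuous outcomes make no use of the baseline score

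*Protocol article*

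**What the plan says.** Section 2.6 lists what each patient completes at enrolment: after sociodemographic data and health status come "NOSE questionnaire, WHO-5 questionnaire, HAD questionnaire, FSS questionnaire, MoCA questionnaire, ESS questionnaire and ISI questionnaire". The same section returns to these at the end of follow-up: "At the 6-month follow-up, all patients will be asked to complete the functional outcomes questionnaires once again". Each of the seven scales therefore has a baseline and a month-6 value for the same patient.

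Section 2.3.4 defines the secondary outcome as functional status at month 6. It does not define it as change from baseline.

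Section 2.7 gives the methods. For two, or for three or more, categories of a normally distributed variable, "independent Samples t-test and ANOVA test will be used, respectively". Non-normal variables go to Mann-Whitney or Kruskal-Wallis, and categorical ones to Pearson chi-square or Fisher's exact test. No ANCOVA, regression, paired test or change-score analysis is named, and no test is tied to a particular outcome.

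The trial has 30 patients per arm: each patient will "be randomly assigned to either the usual care (n = 30) or the TPE group (n = 30". The significance threshold is 0.05, with sidedness not stated.

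**The concern.** The plan collects, for each scale, a covariate that can be expected to predict the month-6 value, and then names only tests that leave it out. In a trial of 60 patients this matters more than usual, because the difference between arms is imprecise to begin with and part of that imprecision is variation between patients that was already present at enrolment.

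The hypothesis at the end of section 1 covers treatment outcomes as well as adherence, and the functional scales bear much of that second part. A real benefit of moderate size could be missed on these scales although the data to estimate it more sharply are on file. Naming the adjustment now also avoids having to decide on it later, once any baseline imbalance has been seen.

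**Working it through.** **Inputs from the article.** 30 per arm, 60 in total (sections 2.2 and 2.6); alpha 0.05 (section 2.7).

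**Assumptions.** Two-sided testing. A difference of 0.5 SD, as illustration only. A correlation r between enrolment and month-6 scores of 0.3 to 0.7. The article gives no correlation, SD, effect size or power for any scale, so it has no figure of its own to reproduce.

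**Formulas**

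- Variance of the ANCOVA estimate relative to the unadjusted comparison: 1 − r². The share of precision (1/variance) lost by leaving baseline out is therefore r².
- Net of the cost of estimating the slope with N = 60: 1 − (1 − r²)(1 + 1/(60 − 4)) = 1 − (1 − r²)(57/56).
- Reduction in standard error: 1 − √(1 − r²).
- Patients per arm that an unadjusted test needs to match ANCOVA with 30: 30/(1 − r²).
- Power: noncentral t with noncentrality (0.5/√(1 − r²)) × √(30/2). Without adjustment this is 0.5 × √15 = 1.94, giving 48%.

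| r | precision lost | net at N = 60 | SE reduction | unadjusted n per arm to match | power, 0.5 SD |
|---|---|---|---|---|---|
| none | – | – | – | 30 | 48% |
| 0.3 | 9% | 7% | 5% | 33 | 51% |
| 0.5 | 25% | 24% | 13% | 40 | 59% |
| 0.6 | 36% | 35% | 20% | 47 | 66% |
| 0.7 | 49% | 48% | 29% | 59 | 76% |

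A simulation with 30 per arm, normal data and 20,000 runs gave variance reductions of 7% (r = 0.3), 24% (r = 0.5) and 47% (r = 0.7), in line with the net column.

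**Detectable difference.** The unadjusted t-test reaches 80% power at about 0.74 SD. With ANCOVA this falls to about 0.70 SD (r = 0.3), 0.64 SD (r = 0.5) and 0.59 SD (r = 0.6).

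**Change scores as an alternative reading.** If the listed tests were applied to change from baseline, the variance ratio to the raw comparison would be 2(1 − r): 1.4 at r = 0.3, 1.0 at r = 0.5, 0.8 at r = 0.6 and 0.6 at r = 0.7. Change scores thus gain nothing at r of 0.5 or below. ANCOVA has the smaller variance throughout, because (1 − r²)/(2(1 − r)) = (1 + r)/2, which is below 1.

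**Chance imbalance.** The standard error of a baseline difference between arms is √(2/30) = 0.26 SD. On average, r times a given imbalance carries into the month-6 difference. For an imbalance of one standard error this is about 0.08 SD at r = 0.3, 0.13 SD at r = 0.5 and 0.18 SD at r = 0.7.

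**The case against.** **The list is generic.** Section 2.7 assigns no test to any outcome and does not say that raw month-6 scores are compared, and an analysis plan that is not shown may add adjustment. It is true that the assignment is inferred. But the outcome is defined as status at month 6, and the two-arm tests named for a continuous score are the t-test and Mann-Whitney. The change-score reading does not rescue the plan, since it is no more precise than the raw comparison at r of 0.5 or below. The section commits to named methods, down to the normality test and software version, so the point concerns the methods chosen and not something left out.

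**The size is unknown.** A reader might infer from a mid-range correlation that a quarter to a third of the precision is wasted. The documents do not support that as a fact: it needs r of about 0.50 to 0.58, and even there the standard error falls by only 13% to 18%. At r = 0.3 the gain in power is three percentage points. This objection stands, which is why the loss is given as r² over a range. It would also differ by scale.

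**The unadjusted tests are not wrong.** This stands too. Under randomisation they are valid, and their standard error already allows for chance imbalance. A reader might infer that the results would be biased, or that an imbalance passes in full into the month-6 difference. Neither follows.

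**Snoring.** It is a functional outcome that the enrolment list does not name, so a reader might infer that it has no baseline. That is not established: section 2.6 says that patients complete the functional questionnaires "once again", which implies an earlier round, and the schedule and flow figures are not shown.

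**Bounded scales.** Linear ANCOVA may fit skewed scores poorly, and the nonparametric route in section 2.7 shows that the authors expect some. This is fair, and the change proposed below allows for it.

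**Conclusion.** The point holds as one of lost efficiency in secondary outcomes. Seven scales have a baseline that the named tests for continuous outcomes, read naturally, leave unused. The precision given up is r²: about 9% to 49% for an assumed r of 0.3 to 0.7. Power for an assumed 0.5 SD difference would rise from 48% to between 51% and 76% over that range. These figures rest on 30 evaluable patients per arm, two-sided testing at 0.05, roughly normal data and a linear relation between baseline and month-6 score. Loss to follow-up would lower all the power figures.

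It is not a finding of bias, it does not touch the primary adherence outcome, and it does not establish that snoring lacks a baseline. The change is worth making because the data are already planned and the adjustment costs almost nothing.

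**What to change.** In section 2.7, name as the main analysis of each of the seven scales an ANCOVA of the month-6 score on arm plus the baseline score of the same scale, reporting the adjusted mean difference with its 95% confidence interval. HADS anxiety and depression each take their own baseline subscale score. Where residuals are clearly non-normal, use a rank-based ANCOVA or a bootstrap confidence interval. Keep the t-test or Mann-Whitney as supportive. If an expected gain is quoted, give it as r² with a stated range of r.

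For snoring, confirm whether the question is asked at baseline. If it is, analyse the three-level outcome with an ordinal model that adjusts for the baseline category.

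The cost is revised analysis wording and slightly more analysis work. For the seven scales no visit, patient or questionnaire is added, and SPSS 23, the package named in section 2.7, fits ANCOVA and ordinal models.
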